## Abstract

**Introduction:**

Neurogenic lower urinary tract dysfunction (NLUTD), including neurogenic detrusor overactivity (NDO) and detrusor sphincter dyssynergia, is one of the most frequent and devastating sequelae of spinal cord injury (SCI), as it can lead to urinary incontinence and secondary damage such as renal failure. Transcutaneous tibial nerve stimulation (TTNS) is a promising, non-invasive neuromodulatory intervention that may prevent the emergence of the C-fibre evoked bladder reflexes that are thought to cause NDO. This paper presents the protocol for TTNS in acute SCI (TASCI), which will evaluate the efficacy of TTNS in preventing NDO. Furthermore, TASCI will provide insight into the mechanisms underlying TTNS, and the course of NLUTD development after SCI.

**Methods and analysis:**

TASCI is a nationwide, randomised, sham-controlled, double-blind clinical trial, conducted at all four SCI centres in Switzerland. The longitudinal design includes a baseline assessment period 5–39 days after acute SCI and follow-up assessments occurring 3, 6 and 12 months after SCI. A planned 114 participants will be randomised into verum or sham TTNS groups (1:1 ratio), stratified on study centre and lower extremity motor score. TTNS is performed for 30 min/day, 5 days/week, for 6–9 weeks starting within 40 days after SCI. The primary outcome is the occurrence of NDO jeopardising the upper urinary tract at 1 year after SCI, assessed by urodynamic investigation. Secondary outcome measures assess bladder and bowel function and symptoms, sexual function, neurological structure and function, functional independence, quality of life, as well as changes in biomarkers in the urine, blood, stool and bladder tissue. Safety of TTNS is the tertiary outcome.

**Ethics and dissemination:**

TASCI is approved by the Swiss Ethics Committee for Northwest/Central Switzerland, the Swiss Ethics Committee Vaud and the Swiss Ethics Committee Zürich (#2019-00074). Findings will be disseminated through peer-reviewed publications.

**Trial registration number:**

NCT03965299.

Strengths and limitations of this studyThis study is a nationwide, randomised, sham-controlled, double-blind clinical trial conducted at all four spinal cord injury (SCI) centres in Switzerland.Transcutaneous tibial nerve stimulation (TTNS) is a well-tolerated, low-risk, non-invasive intervention.The inpatient setting facilitates study procedures and monitoring that maximise intervention adherence.Secondary outcomes provide valuable information regarding the impact of TTNS on additional factors that are relevant to patients as well as clinicians, and also facilitate targeted analyses aimed at better understanding the mechanism underlying TTNS therapy, and the development of neurogenic lower urinary tract dysfunction after SCI.In comparison to beginning immediately after SCI, the intervention start at 29–40 days after SCI (in order to complete all baseline assessments) may modestly reduce the potential for neuroplasticity and the maximum achievable intervention effect.

## Introduction

Most patients with spinal cord injury (SCI) progressively develop neurogenic lower urinary tract dysfunction (NLUTD),^1^ which is one of the most devastating sequelae of SCI. Recovery of lower urinary tract (LUT) function is often identified as a top patient concern after SCI, and sometimes is even prioritised above walking.^2–4^ The consequences of NLUTD, including urinary incontinence, dependence on catheters and recurrent urinary tract infections, negatively impact quality of life (QoL).^5–7^ On a neurological level, intact pathways between the brain and the LUT are required for the complex multilevel neural network governing the LUT to function properly.^8^ SCI is thought to trigger neuroplastic changes in C-fibre-mediated spinal reflex pathways in the spinal cord, which lead to the emergence of aberrant micturition reflexes.^9 10^ Thus, within a few weeks after acute SCI, most patients start experiencing involuntary bladder contractions, neurogenic detrusor overactivity (NDO), which can cause urinary incontinence.^8^ Furthermore, NDO, in combination with detrusor sphincter dyssynergia (DSD) and/or low bladder compliance, can produce high intravesical pressure, which is a relevant risk factor for renal failure.^11 12^ NDO also predisposes patients to vesicoureterorenal reflux, which can endanger the upper urinary tract (UUT).^8 13^ Accordingly, the current urological management approach is centred around protecting the UUT and treating long-term complications of NLUTD.^13 14^ Antimuscarinic medication and intradetrusor onabotulinumtoxin A injections are the first-line and second-line treatments for NDO, but both treatments are often discontinued due to limited effectiveness and bothersome side effects.^15–17^ If conventional conservative and minimally invasive therapies fail, the only remaining options are more invasive treatments which are associated with substantial morbidity, such as bladder augmentation and urinary diversion.^18 19^ While neurourological treatment of patients with SCI has greatly improved during the last decades, it is only applied when NLUTD is already established with little chance of recovery.

Here, we present the protocol for a randomised controlled trial (RCT) that aims at producing evidence for the use of non-invasive electrical stimulation (neuromodulation) to prevent the development of NDO. Early neuromodulatory therapy has the potential to impede or alter neuroplasticity, preventing the sensitisation of ‘silent’ C fibres and the formation of spinal reflex pathways thought to be responsible for NDO. Indeed, in a pilot study, bilateral sacral neuromodulation during the early phase of SCI prevented the development of NDO and also improved erectile and bowel function.^20^ Furthermore, in animal models, early neuromodulatory interventions after SCI can modulate the micturition reflex^21^ and inhibit detrusor overactivity.^22^ In humans, non-invasive neuromodulatory techniques such as tibial nerve stimulation^23^ and transcutaneous electrical nerve stimulation (TENS)^24^ have shown promise in a treatment context^25–28^ and warrant well-designed RCTs. Transcutaneous tibial nerve stimulation (TTNS) has generated interest, as a neuromodulatory treatment that is completely non-invasive (current is applied through surface electrodes) with no known safety risks, easy to apply and well accepted by patients. A randomised pilot trial in patients with acute SCI concluded that TTNS was feasible and safe in an inpatient rehabilitation setting.^29^ Furthermore, at the end of the study, the participants in the intervention group had lower detrusor pressures and fewer developed DSD compared with the sham group,^30^ suggesting that TTNS could alter the course of NLUTD. We hypothesise that TTNS applied in the acute phase after SCI will prevent the emergence of C-fibre evoked bladder reflexes, thereby the development of NDO, and avert UUT damage and urinary incontinence. TTNS in acute SCI (TASCI) aims to provide evidence regarding the clinical efficacy of TTNS as a preventative measure for NDO, along with additional insight into the mechanism underlying TTNS and the course of NLUTD development during the first year after SCI. We operationalised this RCT as a population-based study in the context of specialised rehabilitation for SCI in Switzerland.

## Methods and analyses

This protocol follows the recommendations of the Standard Protocol Items: Recommendations for Interventional Trials (SPIRIT) Statement (online supplementary 1).^31^

10.1136/bmjopen-2020-039164.supp1Supplementary data

### Study design and setting

TASCI is a nationwide, randomised, sham-controlled, double-blind clinical trial investigating the effects of TTNS in patients with acute SCI.^32^ The intervention will take place during the inpatient rehabilitation stay in one of the four SCI centres in Switzerland (Basel: REHAB Basel, Nottwil: Swiss Paraplegic Center, Sion: Clinique romande de réadaptation, and Zürich: Balgrist University Hospital). Furthermore, TASCI is nested in the inception cohort of the prospective Swiss Spinal Cord Injury (SwiSCI) cohort study.^33^

The TASCI schedule (figure 1) includes a screening and baseline period from days 5–39 after SCI diagnosis, followed by a 6–9 weeks intervention period that ends when all 3-month follow-up assessments have been completed. Three follow-up visits are planned: the 3-month visit (day 91±10), 6-month visit (day 182±10) and 12-month visit (day 365±10). The 1 year post-SCI measurement time point was chosen for the primary outcome variable because it represents the time when the patient’s situation is stable enough to start considering invasive treatment options.^14^ The additional time points were selected to maximise the chances of detecting treatment effects, as well as to coincide with routine follow-up assessments of patients with SCI.

**Figure 1 F1:**
[figure not shown]
Trial flow chart. Safety data will be recorded on a continuous basis the entire time the participant is enrolled in the study. *Additional clinical assessments target urological and bowel function and symptoms, neurological structure and function, sexual function, spasticity, functional independence, quality of life and biochemical and molecular biomarkers in the urine, blood, stool and in bladder tissue (additional consent required for bladder biopsy). **Histomorphology is based on bladder biopsy which requires additional consent. DO, detrusor overactivity; SCI, spinal cord injury; TTNS, transcutaneous tibial nerve stimulation.

### Participants

All patients with SCI admitted to rehabilitation in one of the participating centres are screened for eligibility using information from their routine clinical examinations. For a full listing of inclusion and exclusion criteria, refer to table 1. Eligible patients are then approached by an investigator or supervising clinician who obtains informed consent. For an English translation of the study information leaflet and declaration of consent, see online supplementary 2. Patients who consent undergo additional baseline assessments and are randomised after their eligibility for the trial has been confirmed.

10.1136/bmjopen-2020-039164.supp2Supplementary data

**Table 1 T1:** Transcutaneous tibial nerve stimulation in acute spinal cord injury (TASCI) eligibility criteria

Inclusion criteria	Exclusion criteria
Age ≥ 18 years Patients with acute SCI (traumatic SCI and sudden onset (<7 days) non-traumatic SCI), within 40 days after injury Patients with acute SCI at cervical or thoracic level Willingness to take part and follow the requirements of the protocol during TASCI (up to 1 year after SCI): No percutaneous tibial nerve stimulation No functional electrical stimulation (FES) apart from upper limb FES No electrical muscle stimulation Informed consent	Contraindications to the investigational product Treatment with antimuscarinics or mirabegron DO with contractions greater than 40 cm H_2_O at a bladder filling volume of less than 500 mL at baseline visit Known or suspected non-adherence, drug or alcohol abuse Inability to follow the procedures of the study, for example, due to language problems, psychological disorders, dementia, and so on, of the participant Participation in another study with investigational drug or product within the 30 days preceding and during the present study Neuromodulation treatment for urological or bowel indication in the last 6 months or ongoing Botulinum toxin injections in the detrusor and/or urethral sphincter in the last six months Bilaterally absent tibial nerve compound muscle action potential (amplitude < 1 mV) Women who are pregnant or breast feeding Individuals especially in need of protection (according to Research with Human Subjects published by the Swiss Academy of Medical Sciences (www.samw.ch/en/News/News.html) Enrolment of the investigator, their family members, employees and other dependent persons Pre-existing or concomitant medical condition apart from SCI that might pose a safety issue or would interfere with interpretation of study results or study conduct (eg, Parkinson’s disease, neurodegenerative disorders including multiple sclerosis and amyotrophic lateral sclerosis, urological malignancies)

Urinary tract infection (UTI) is a transitory exclusion criterion for all functional assessments, including urodynamics. Before undergoing functional assessments, participants are screened for UTIs and haematuria. If a UTI is identified, treatment is initiated, and the functional assessments are rescheduled once the participant has been symptom free for at least 3 days.

DO, detrusor overactivity; SCI, spinal cord injury.

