### Outcomes

The primary outcome is the occurrence of NDO jeopardising the UUT up to 12 months after SCI, that is, at 1 year after SCI or any earlier time point if NDO treatment is needed. This outcome is a composite measure including: NDO with an amplitude ≥40 cm H_2_O identified during urodynamic investigation; or else the initiation of NDO treatment with antimuscarinics and/or intradetrusor onabotulinumtoxin A injections. Urodynamics will be performed before starting TTNS (within 40 days after SCI) at follow-up visits 3 months, 6 months and 1 year after SCI, or at any earlier time point if there is reason to believe that the participant has developed NDO, before starting NDO treatment.

Secondary outcomes (table 2) were selected to further evaluate the effects of the TTNS intervention, and include clinical outcomes such as differential changes in LUT and bowel function and symptoms, sexual function, neurological function, as well as functional independence and QoL. Moreover, the evaluation of differential changes in brain and spinal cord function as well as corticospinal integrity, and biomarkers in the urine, blood, stool and bladder tissue will also provide insight into the mechanism of action underlying the TTNS intervention. All secondary outcomes may also be used to better understand the pathogenesis of NLUTD after SCI. Information collected will provide a detailed description of the disease course, and when possible, inform prognostic modelling and address causal questions. Finally, adverse events will be recorded for the duration of the participant's enrolment in the study to evaluate the safety of TTNS. Table 2 shows an overview of the secondary outcome measurement tools and assessment periods, and secondary outcome parameters are listed in detail in online supplementary 3.

10.1136/bmjopen-2020-039164.supp3Supplementary data

**Table 2 T2:** Secondary outcome measurement tools and time of assessment

Outcome and assessment tool	Assessment periods
Occurrence of neurogenic DO jeopardising the upper urinary tract over a 1-year time course (time-to-event analysis)	
Urodynamic investigation	S&B, 3M, 6M, 12M
Clinical assessment	S&B, 3M, 6M, 12M
Differential changes in lower urinary tract function	
Urodynamic investigation	S&B, 3M, 6M, 12M
Differential changes in lower urinary tract symptoms	
Bladder diary	S&B, 3M, 6M, 12M; TTNS: biweekly
International Prostate Symptom Score (IPSS)	S&B, 3M, 6M, 12M; TTNS: weekly

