### Statistical analyses

The primary analysis will be an intention-to-treat analysis. The general statistical methodology for primary and secondary outcomes comprises basic descriptive statistics and multivariable regression analyses. Continuous variables will be tested for normality, and displayed as either means and SD or medians and ranges; categorical variables will be displayed as frequencies and proportions. Multivariable regression techniques will be employed to control for possible confounding due to unequal distribution of baseline parameters across the trial arms, as well as systematic variation in outcomes across RCT strata, that is, centre and LEMS. Longitudinal analysis techniques (eg, mixed-effect models, structural equation models for growth and time-to-event models) will be used to account for repeated measures, facilitating time-updated covariate adjustment and appropriately modelling trends with respect to time.

The primary outcome ‘the occurrence of NDO jeopardising the UUT 1 year after SCI’ is a binary response variable, which will be described using proportions with 95% binomial CIs and analysed using logistic regression, thus expressing treatment effect sizes as ORs (with 95% CIs). Sensitivity analyses will include a time-to-event analysis to evaluate the impact of TTNS on the risk of early drop-out or preterm endpoints (<1 year). Protocol non-adherence, early withdrawals and loss to follow-up will be examined and used to inform per-protocol sensitivity analyses. Subgroup analyses stratified on LEMS or study centre may be performed if an intervention–subgroup interaction is found, with the understanding that these analyses will likely be underpowered. In cases where outcome data are used in an observational context, usually to examine prognosis or NLUTD aetiology, causal claims will be supported by an underlying theoretical framework.

Multiple imputation will be used when appropriate to account for missing data in the predictor variables.^38^ Pattern mixture models may be applied to address missing outcome data for different scenarios of the missing data process.^39^ Sensitivity analysis will be used to evaluate the robustness of the chosen imputation strategy. Any sensitivity analyses added after the breaking of the blind (post-hoc sensitivity analyses) will be clearly identified as such in the trial report.

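### Detrusor overactivity of 40 cm H2O or less at baseline does not bar entry, so the primary comparison does not by itself show that NDO was prevented from emerging, and baseline DO is not a fixed covariate

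*Protocol article*

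**What the plan says.** All references are to the protocol article.

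- **Hypothesis (Introduction).** TTNS given early "will prevent the emergence of C-fibre evoked bladder reflexes, thereby the development of NDO". No amplitude limit is attached. The Sample size section likewise counts participants who develop NDO, again without an amplitude.
- **Entry (Participants, Table 1).** The only exclusion on baseline bladder contractions is "DO with contractions greater than 40 cm H_2_O at a bladder filling volume of less than 500 mL at baseline visit". Patients already on antimuscarinics or mirabegron are excluded separately.
- **Timing.** The Introduction says that NDO begins in most patients within weeks of the injury. The Study design section sets "a screening and baseline period from days 5–39 after SCI diagnosis".
- **Primary outcome (Outcomes).** NDO jeopardising the upper urinary tract, as a composite. The amplitude limb is "NDO with an amplitude ≥40 cm H_2_O identified during urodynamic investigation". The treatment limb, which carries no amplitude limit, is worded "or else the initiation of NDO treatment with antimuscarinics and/or intradetrusor onabotulinumtoxin A injections". Urodynamics are also done before TTNS starts.
- **Analysis (Statistical analyses).** Logistic regression giving an odds ratio. Multivariable models are to handle baseline parameters that turn out unequally distributed between arms, and "systematic variation in outcomes across RCT strata, that is, centre and LEMS". On subgroups: "Subgroup analyses stratified on LEMS or study centre may be performed if an intervention–subgroup interaction is found".

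**The concern.** The stated aim is that the aberrant reflex does not arise. A patient who enters with involuntary contractions of, say, 30 cm H2O already has it. For that patient the amplitude limb measures progression to 40 cm H2O or more. The treatment limb can be met by starting a drug for NDO that has not changed since entry. By the protocol's own account of timing, such patients need not be rare when baseline runs to day 39, although no prevalence is given.

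Two things follow. First, a positive result could come from fewer new cases of NDO, from dampening of NDO already present, or from both, and the primary odds ratio cannot tell these apart. Second, baseline DO is a plausible predictor of the outcome and is measured in advance, yet it would enter the model only if it happened to be unequal between arms. Choosing a covariate by observed imbalance makes the primary model depend on the data, and it gives up precision when the arms happen to be balanced.

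**Working it through.** **1. The passages side by side**

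| Element | NDO meant |
|---|---|
| Hypothesis | any NDO, its emergence |
| Sample size text | any NDO, its development |
| Exclusion at entry | contractions above 40 cm H2O at a volume below 500 mL |
| Outcome, amplitude limb | 40 cm H2O or more |
| Outcome, treatment limb | start of treatment, no amplitude |

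A participant with baseline DO below 40 cm H2O is free of the amplitude event at entry, so that limb is a valid new event. The treatment limb is a new event as a treatment start, but the NDO being treated may predate randomisation.

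**2. The plan's own figure**

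Inputs from Sample size: success 0.15 (sham) and 0.15 + 0.25 = 0.40 (verum), power 0.80, alpha 0.05 (sidedness not stated; two-sided used), continuity correction. The mean proportion is 0.275.

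Uncorrected n per arm = [1.96·√(2·0.275·0.725) + 0.842·√(0.15·0.85 + 0.40·0.60)]² / 0.25² = 48.9.

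Corrected n = (48.9/4)·[1 + √(1 + 4/(48.9·0.25))]² = 56.6, so 57 per arm and 114 in total. The stated number reproduces exactly, and this point does not touch it.

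Corrected power at n = 57 is Φ{[(|d| − 1/n) − 1.96·√(2p̄(1−p̄)/n)] / √((p₁q₁ + p₂q₂)/n)} = Φ[(0.2325 − 0.1639)/0.0803] = Φ(0.853) = 0.803.

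**3. Dilution, as illustration only**

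Assume that a share s has baseline DO, that sham success is 0.15 in both groups, that the effect is 0.25 without baseline DO, and that it is d₂ with it. Then d = (1 − s)·0.25 + s·d₂. The documents give neither s nor d₂.

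| s | d₂ | d | Corrected power, 57 per arm |
|---|---|---|---|
| 0.2 | 0 | 0.20 | 0.62 |
| 0.4 | 0 | 0.15 | 0.39 |
| 0.2 | 0.10 | 0.22 | 0.70 |
| 0.4 | 0.10 | 0.19 | 0.57 |
| any | 0.25 | 0.25 | 0.80 |

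**4. Gain from adjustment, also under assumptions**

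Simulated trials (about 3000 per setting) with 57 per arm and outcome proportions 0.85 and 0.60, analysed by logistic regression without and with baseline DO:

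| Prevalence of baseline DO | OR for outcome | Unadjusted | Adjusted | Gain |
|---|---|---|---|---|
| 30% | 3 | 0.851 | 0.865 | 0.014 |
| 30% | 6 | 0.857 | 0.885 | 0.028 |
| 50% | 6 | 0.860 | 0.897 | 0.037 |

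These are powers of the logistic test, without continuity correction. They should not be set against the 0.80 of steps 2 and 3.

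**5. Moving the claim to DO-free participants**

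With s = 0.4, 0.6·57 ≈ 34 per arm remain, and corrected power for 0.15 against 0.40 is 0.53. With s = 0.2, about 45 per arm remain and power is 0.68.

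**The case against.** **The outcome is already narrower than emergence.** It is titled NDO jeopardising the upper urinary tract, and preventing that in someone with weak DO is prevention of the named outcome. This stands. The mismatch lies in the hypothesis and sample size wording and in the treatment limb, not in the validity of the comparison.

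**Covariates and subgroups belong to the analysis plan, which is not shown.** This stands in part. A reader might infer that neither the model nor the reporting will ever separate these patients. The article does not support that: unequal baseline parameters could include baseline DO, and the baseline tables and full covariate list may sit in documents that are not shown. What the article does state is the rule that adjustment beyond centre and LEMS follows observed imbalance, and that rule can be judged as written.

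**The power loss is assumed.** A reader might infer that the trial is underpowered, with power as low as 0.39. That needs a prevalence that the documents do not give and no effect at all where DO exists, whereas the Introduction reports promise for tibial nerve stimulation as a treatment. It also reads the planned 0.25 as applying only to DO-free patients, whereas Sample size states it for the trial's participants. The objection stands.

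**Baseline DO as the strongest predictor is undocumented.** This also stands. The Randomisation section calls LEMS the primary prognostic indicator, although it bases this on a model for continence and bladder emptying rather than detrusor pressure. It is enough here that baseline DO is a plausible predictor.

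**Conclusion.** The point holds as one of interpretation and model specification. Patients with DO of 40 cm H2O or less at baseline are eligible, and the treatment limb can count NDO present at entry. The primary comparison remains unbiased and tests prevention of NDO jeopardising the upper urinary tract, but it does not by itself show that NDO was prevented from emerging. A reader might infer bias, or an invalid primary outcome; neither follows.

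In numbers, a fixed covariate gains about 1 to 4 power points under an assumed prevalence of 30–50% and odds ratios of 3–6. The dilution loss cannot be computed from the documents. It ranges from nothing, if the effect is equal, to the assumed values tabulated above. The case for change therefore rests on a clearer claim and on a model fixed in advance at almost no cost, not on rescuing power.

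A separate boundary mismatch is visible in the table: the exclusion uses more than 40 cm H2O with a volume limit, while the outcome uses 40 cm H2O or more without one. The two passages should be reconciled. Which threshold is right is not judged here, and the conclusion above does not depend on it.

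**What to change.** 1. Prespecify baseline DO, taken from the urodynamics done before TTNS (absent or present, or maximum amplitude), as a fixed covariate in the primary logistic model alongside centre and LEMS, whatever imbalance is observed.
2. Reconcile the hypothesis and sample size wording with the Outcomes section, so that the trial-level claim is NDO of amplitude 40 cm H2O or more, or start of NDO treatment.
3. Report the treatment effect with its confidence interval by baseline DO status, labelled supportive and descriptive. Do not move the main claim to DO-free participants: at 34 per arm the corrected power would be 0.53.

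The cost is text in the protocol or analysis plan, one extra model parameter (more if amplitude is modelled flexibly), and wide intervals in the two groups. No new data are needed, and no eligibility or treatment rule changes. The choice should be fixed before unblinding.
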